## Abstract

**Background:** Transurethral resection of the prostate (TURP) is regarded as the “gold standard” for the treatment of benign prostatic hyperplasia (BPH) in elderly men. However, ~15% of patients who had undergone TURP had intraoperative and postoperative complications, such as bleeding, urinary incontinence and urethral stricture. Transperineal percutaneous laser ablation (TPLA) is a method that places the optical fibre directly into the prostate with the guidance of ultrasound imaging, and the percutaneous transperineal approach is performed distal to the urethra and rectum to protect these structures and reduce urethral or postoperative infection. Several studies on TPLA for BPH treatment have been reported recently; however, high-quality randomised controlled trial (RCT) to evaluate its efficacy, safety, and long-term follow up remain absent.

**Methods:** This study is a multicentre, open-label RCT to assess the efficacy and safety of TPLA vs. TURP to treat BPH. We hypothesise that the TPLA has non-inferior efficacy to TURP in the International Prostate Symptom Score (IPSS) at 3 months changing from the baseline and lower incidence of post-surgery complications. One hundred and fourteen patients with BPH will be recruited at 19 sites and randomly assigned at 1:1 to TPLA or TURP groups. The patients will be followed up at 1, 3, 6, 12, and 24 months after the procedure.

**Discussion:** The study will be the first multicentre clinical trial including 16 participating centres in China, Italy, Switzerland, and Poland with relatively large sample size 114. By comprehensively compare the safety and efficacy of TPLA with TURP in patients with BPH, especially concerning the improvement of lower urinary tract symptoms (LUTS) and complication incidence, the study will help to illustrate the clinical value of TPLA and provide a beneficial alternative treatment for BPH patients.

**Clinical Trial Registration:** The study has been registered on Chinese Clinical Trial Registry (http://www.chictr.org.cn), identifier [ChiCTR1900022739].

## Introduction

Benign prostatic hyperplasia (BPH) is a common urologic disease in elderly men. Approximately 50% of men >50 years of age will have pathological evidence of BPH, with this number increasing to >80% as men reach their eighth decade of life and older (1–3). The series of clinical manifestations, such as urinary frequency, urgency and incontinence caused by BPH, are collectively referred to as lower urinary tract symptoms (LUTS) which brings many inconveniences to elderly patients' life and the decline of life quality (4–6).

Treatment options of BPH start at watchful waiting and progress through medical to surgical interventions, depending on the patients' symptoms. Currently, surgery has become the main treatment method with the progression of BPH in addition to drug therapy. Although transurethral resection of the prostate (TURP) is regarded as the “gold standard” for the minimally invasive treatment of BPH (7–9), many intraoperative and postoperative complications persist in TURP (10, 11), depending on the surgeon expertise, such as the urinary incontinence or iatrogenic injury caused by operation (12–14). The tissue on the cut surface forms an eschar, whose organisational structure is fuzzy, leading to injury even perforation of the surgical capsule. In addition, the eschar may bring about secondary haemorrhage (15) after shedding and repeated haematuria after the operation. And the high temperature of TURP can cause urethral burn and postoperative urethral stricture (16–21).

With the emergence of various intracavitary minimally invasive devices, new technologies are being applied to the medical field, such as transurethral enucleation of the prostate (TUEP), which including plasma kinetic enucleation of the prostate (PKEP), holmium laser enucleation of prostate (HoLEP), thulium laser enucleation of the prostate (ThuleP) and some other laser based methods (22). Lasers show better haemostatic effects and cause less bleeding during operations (23–26). Additionally, lasers are non-conductive; thus, they can be applied in patients with heart pacemakers and other electric implants. Although these new techniques might offer sufficient efficacy and lower risk of complications over standard bipolar-TURP (27, 28), However, the levels of evidence are too low and follow-up still too short to offer solid recommendations, and larger comparative studies are needed to evaluate the ultimate impact of the en-bloc approach on postoperative outcomes (22, 29). And since the surgical approach are transurethral avoiding injury is challenging, and haematuria and urethral stricture may occur after the operation (30–33).

With the guidance of high-frequency transrectal ultrasound (TRUS), which is widely used in the diagnosis and treatment of BPH, the clinician can accurately locate the position of the lesion in the prostate and guide the puncture through the image in real time. The percutaneous transperineal approach occurs distal to the urethra and rectum, to protect these structures and reduce the difficulty of preoperative preparation and operation, and lower postoperative infection effectively (34).

Can laser treatment of prostate guided by TRUS achieve the minimally invasive treatment of BPH using a percutaneous transperineal approach? Researchers have verified transperineal percutaneous laser ablation (TPLA) a feasible and safe method (35–40). Pacella CM conducted a single arm trial, performed the analysis on 160 patients with 6 months follow and 83 patients with 12 months after TPLA (41), and de Rienzo G conducted TPLA for 21 patients, verified the significant advantage in Qmax, IPSS, and peculiar ability to preserve ejaculation (38). However, high-quality RCTs, compared with TURP, the most widely used surgical method and “gold standard” for BPH patients, remained absent. Additionally, the efficacy and safety should be illustrated by a longer follow-up time.

This study aims to evaluate the following: the efficacy and safety of TPLA to treat BPH compared with TURP; to explore the clinical value including the prognosis and curative effect of TPLA after long-term follow-up; to seek scientific advice to optimise the relevant parameters and precautions of TPLA treatment and; to provide evidence for the indication of TPLA by analysing the advantages and disadvantages in subgroups.

## Methods and Analysis

### Study Design

This study is a multicentre, open-label, randomised controlled clinical trial. This study protocol follows the standard protocol for clinical trials in accordance with the SPIRIT 2013 statement and follows the CONSORT statement for clinical trial transparency (42, 43). The study is registered on Chinese Clinical Trial Registry (http://www.chictr.org.cn), registration number: ChiCTR1900022739. The study was approved by the Independent Ethics Committee of Shanghai Jiao Tong University Affiliated Sixth People's Hospital (Ethics number: 2018-034) and the local ethics committee of participating centres.

### Objective and Hypothesis

The primary objective of the study is to assess the efficacy and safety of TPLA vs. TURP in treating BPH. We hypothesise that TPLA has non-inferior efficacy to TURP according to the IPSS score change at 3 months from baseline and lower incidence of post-surgery complications. Secondary endpoints, including the maximum urinary flow rate, patients' quality of Life (QoL) and post-urination residue, operation time and hospitalisation time, will also be assessed.

The secondary objective is to determine the optimal target population in patients with BPH for TPLA treatment.

### Participants

#### Patient Recruitment

The participants will be recruited from patients with BPH at Shanghai Sixth People's Hospital and other participating centre hospitals. Patients with LUTS and imaging-confirmed BPH and who are willing to accept surgical treatment could be recommended by clinicians, sonographers or advertisement, and instant messaging software (WeChat). The subject diagram is presented in Figure 1. Before the recruitment the research staff would introduce the two operation methods (TPLA and TURP) including the strengths and drawbacks, respectively, to the participants, and clarify the risks and potential benefits of participating the trial. The screening and randomisation procedure, the operation, hospitalisation, and the follow-up details would be fully discussed as well. And written informed consent will be obtained before eligibility screening. The participants can decide to withdraw their consent for any reason during the entire study. The results of follow-up will be disseminated to the study participants through paper reports and telephone communication.

**Figure 1 F1:**
[figure not shown]
Subject diagram. The flow diagram of this randomised controlled trial.

#### Patient Screening

Eligibility screening will be performed in 14 days before surgery, as listed in Table 1.

**Table 1 T1:** Contents of enrolments, interventions, and assessments.

**Stage**	**Screening**	**Preoperative examination**	**Surgery**	**Hospitalisation**	**Follow-up**				
**Time**	**−14**~−**1 days**	**−7**~−1** days**	**0 day**	**4 ± 3 days**	**1 month**	**3 months**	**6 months**	**12 months**	**24 months**
Informed consent	√								
Medical history	√								
Vital signs		√	√	√					
ECG		√	√	√^*^					
Blood routine	√		√	√^*^					
Urine routine	√		√	√^*^	√	√	√	√	√
Coagulation function	√		√	√^*^					
Liver and kidney function		√	√	√^*^					
Blood electrolyte		√	√	√^*^					
Visual analogue score (VAS) pain score				√(24 h after surgery)					
PSA	√				√	√	√	√	√
Qmax	√				√	√	√	√	√
Urodynamics		√				√			
IPSS	√				√	√	√	√	√
QoL score	√				√	√	√	√	√
EQ-5D score	√				√	√	√	√	√
Transrectal ultrasound	√				√	√	√	√	√
MRI	√					√			
Transabdominal bladder ultrasonography	√				√	√	√	√	√
Sexual function (IIEF-5)	√				√	√	√	√	√
Ejaculatory dysfunction (MSHQ-EjD)									
Operation time			√						
Specific time of resection or ablation			√						
Intraoperative blood loss and blood transfusion records			√						
AE records			√	√	√	√	√	√	√
Catheter retention time				√					
Hospitalisation				√					

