##### Hospitalisation and Observation

After the treatment, the patients should be closely supervised for 2 days with standard post-operation care and the catheter, in the absence of adverse events, is removed within 2 weeks after the procedure.

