### Measurements and Clinical Outcomes

#### Data Collection

The measurements and data collection schedule are presented in Table 1.

The general medical history of each patient will be obtained through interviews and a review of existing medical records. The data collected and recorded include demographics (e.g., age, gender, and race/ethnicity) and meaningful past or current illnesses. A history of known drug allergies, other allergies, or a history of allergic reactions and all concomitant medications (including Chinese medicine) will also be recorded.

Vital signs (heart rate, respiration, and blood pressure), electrocardiograph (ECG), amount of bleeding and laboratory tests (liver and kidney function, routine blood tests, and blood electrolytes) will be evaluated before and after the operation within 24 h, and the operation time, treatment time, intraoperative blood loss, and blood transfusion will be recorded as well. The post-operation observation include urine routine, urine flow rate test, IPSS, transabdominal bladder ultrasonography (residual urine measurement), and TRUS, quality of life QoL score, European five-dimensional health scale (EQ-5D) score, sexual function evaluation International Index of Erectile Function-5 (IIEF-5), Male Sexual Health Questionnaire-Ejaculatory Dysfunction (MSHQ-EjD) score. Enhanced magnetic resonance imaging (MRI) will be performed 3 months after treatment.

Regarding quitting patients, the researchers will collect the medical materials integrally and record their quitting reasons and time.

All of the data collectors and evaluators will be blinded to the group assignments. The data in this trial will be collected using electronic case report forms (eCRFs) using a remote data capture (RDC) system (https://clinicaldata.shsmu.edu.cn/). The RDC system will be provided by the Clinical Research Institute of Shanghai Jiao Tong University School of Medicine (Shanghai, China).

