#### Clinical Outcomes

##### Efficacy Endpoint

The primary efficacy endpoint is the IPSS score change at 3 months from baseline.

The secondary efficacy endpoints include:

IPSS change at 6, 12, and 24 months from baseline.Qmax at 3, 6, 12, and 24 months after treatment.Residual urine volume at 3, 6, 12, and 24 months after treatment.Quality of life score, IIEF-5 score, MSHQ-EjD score (3 item and bother) at 3, 6, 12, and 24 months after treatment.European five-dimensional health scale score EQ-5D at 3 and 6 months after treatment.

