##### Safety Endpoint

The safety endpoint is the incidence of complications within 3 months after surgery (hyponatremia, urinary retention, TURS, erectile dysfunction, bladder neck contracture, urethral stricture, perforation of the prostate capsule, infection, sepsis, urinary incontinence, bladder rupture, haematuria, and persistent bacteriuria for more than 3 weeks after surgery), intraoperative blood loss; VAS pain score; postoperative urinary catheter retention time; surgical success rate.

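### Table 1 does not match two defined endpoints: MSHQ-EjD has no visit ticked and no baseline, and catheter time is scheduled only within day 7 although removal may come up to day 14

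*Protocol article*

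**What the plan says.** The Data Collection section hands the timing of measurements to the table: "The measurements and data collection schedule are presented in Table 1". The Follow-Up section also refers to Table 1 for the collection of the efficacy and safety endpoints.

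**MSHQ-EjD.** The Efficacy Endpoint section names as a secondary endpoint the "MSHQ-EjD score (3 item and bother) at 3, 6, 12, and 24 months after treatment". The Data Collection section includes the "Male Sexual Health Questionnaire-Ejaculatory Dysfunction (MSHQ-EjD) score" among the post-operative observations. In Table 1 (Patient Screening section) the row "Ejaculatory dysfunction (MSHQ-EjD") is present but blank in every column. The row directly above, "Sexual function (IIEF-5"), is ticked at screening and at 1, 3, 6, 12 and 24 months, as are IPSS, QoL and EQ-5D.

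**Catheter time.** The Safety Endpoint section lists "postoperative urinary catheter retention time". The Table 1 row "Catheter retention time" has one tick, in the Hospitalisation column, whose time is 4 ± 3 days. The Hospitalisation and Observation section says that the catheter, if no adverse event occurs, "is removed within 2 weeks after the procedure".

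**The concern.** A site that works from Table 1 would give the ejaculatory questionnaire at no visit, although the text wants it at four. It would also have no instruction to give it before surgery, and a pre-treatment score cannot be recovered afterwards. This is the domain in which the Introduction reports an advantage for TPLA, from a cited series of 21 patients, so a reader will want to see change within patients as well as scores by arm.

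For catheter time, the only scheduled recording point closes before the permitted removal period does. A patient whose catheter comes out after discharge, or after day 7, has no visit at which the value is due. The Statistical Methods section excludes safety endpoints from multiple imputation, and catheter time is listed as one, so the stated analysis would not make good a missing value.

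**Working it through.** There is no planned figure to reproduce here. The check sets the table against the text and compares the time windows.

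**MSHQ-EjD**

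1. Table 1 has nine stage or visit columns: screening, preoperative examination, surgery, hospitalisation, and five follow-up visits. Ticks in the MSHQ-EjD row: 0 of 9. Every other row has at least one.
2. Of the nine, the other questionnaires (IPSS, QoL, EQ-5D, IIEF-5) use six: screening and 1, 3, 6, 12 and 24 months. MSHQ-EjD: 0 of 6.
3. Time points that the Efficacy Endpoint section needs for MSHQ-EjD: 4 (3, 6, 12 and 24 months). Table and text therefore disagree on all four.
4. Baseline: the Data Collection section mentions the score only after the operation, the Efficacy Endpoint section only after treatment, and Table 1 not at all.
5. Cost of having no baseline: the total of 114 gives 114 / 2 = 57 patients per arm. With a baseline-to-follow-up correlation ρ, adjustment for baseline multiplies the variance of the between-arm difference by about 1 − ρ², a reduction of ρ². The document gives no ρ. As an assumption:
   - ρ = 0.3: reduction 0.3² = 0.09, about 9%
   - ρ = 0.7: reduction 0.7² = 0.49, about 49%

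**Catheter time**

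1. Hospitalisation column: 4 − 3 = day 1 to 4 + 3 = day 7.
2. Limit for removal without adverse events: 2 weeks = day 14.
3. Period with no recording point: days 8 to 14, which is 14 − 7 = 7 days. It is longer where an adverse event delays removal.
4. A removal before day 7 is also outside the ticked stage if the patient has already gone home.
5. The next scheduled contact is the 1-month visit, where the catheter row is not ticked.

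**The case against.** The best reply on MSHQ-EjD is that the blank row may not exist in the published table. It is the only empty row, and it sits under IIEF-5, with which the Efficacy Endpoint section pairs it at identical times. A cell shared by the two rows and lost when the PDF was read would look just like this. The missing baseline depends on the same row, because the text gives no baseline for IIEF-5 either; only Table 1 does. This stands as a condition: the first half of the point must be checked against the typeset table and falls if the cell is shared. The catheter half is unaffected.

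Three stronger readings are tempting, and the document does not support them.

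- A reader might infer that MSHQ-EjD is not collected at all. The Data Collection and Efficacy Endpoint sections both commit to it after treatment, so for follow-up this is a conflict between table and text.
- A reader might infer that, without a baseline, existing dysfunction cannot be told apart from a treatment effect. Allocation is random and 1:1, so existing dysfunction is balanced in expectation, and the endpoint as defined needs only post-treatment scores. The between-arm comparison stays valid.
- A reader might infer that catheter time is cut off at discharge, so that removal on day 12 after discharge on day 3 is recorded as 3 days, a 9-day error favouring the arm that goes home earlier. No section sets such a cut-off, the endpoint has no in-hospital limit, and a single tick may only mark the stage to which a duration belongs. The document does not say how many patients leave with a catheter or from which arm.

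It is also fair that a condensed article may leave form-level detail, such as a removal date field, to the full protocol. That does not remove the mismatch between the published schedule and the permitted removal period.

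**Conclusion.** The point holds as a mismatch between Table 1 and two defined endpoints. It does not touch the primary endpoint, the sample size or the primary analysis.

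- **MSHQ-EjD:** as shown, none of the four required visits is scheduled, and no baseline is scheduled anywhere. The loss is within-patient change and precision, about 9% to 49% of variance under the assumed correlations of 0.3 to 0.7. This rests on the blank row being real.
- **Catheter time:** the item is scheduled, but only to day 7 against a permitted day 14. Later or post-discharge values may be missing or truncated. The document supports neither a size nor a direction of bias.

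The baseline is the more urgent part, since it cannot be obtained once a patient has had surgery.

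**What to change.** 1. Check the MSHQ-EjD row in the original Table 1. If it is blank there, tick it at screening and at 3, 6, 12 and 24 months; 1 month is optional, in line with IIEF-5. Analyse the score adjusted for baseline.
2. Reconcile the catheter row of Table 1 with the Hospitalisation and Observation section. Record the calendar date of catheter removal, confirm it at the existing 1-month visit, and compute catheter time from the dates for every patient. No view is taken here on when the catheter should be removed.

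The cost is an edit to the schedule table and the eCRF, one short questionnaire at visits that already take place, and one date field. No visit is added. Patients already operated on would have no baseline MSHQ-EjD, and the report should say how many.

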##### Inclusion Criteria

Patients with LUTS caused by BPH who have failed prior treatment or are unsuitable for medical treatment as judged by the clinician.Male older than 50 years.IPSS score ≥8.Prostate volume measured by TRUS between 30 and 100 ml.A maximum urinary flow rate (Qmax) ≤15 mL/s.Transabdominal bladder ultrasonography: post-urination residue ≥50 ml.Provide Informed consent.

##### Exclusion Criteria

Urethral stenosis.Previous prostate, bladder, or urethral surgery.Dysuria caused by bladder dysfunction.History of a long-term indwelling catheter.BPH with mainly medial lobe hyperplasia (intravesical prostate projection ≥10 mm); transabdominal bladder ultrasonography revealed bladder calculi or obvious bladder tumour.Patients with pathology-proven prostate cancer; Serum prostate specific antigen (PSA) >4 ng/ml and PSAD ≥0.15 ng/ml^2^, no iatrogenic injury.Patients with known neurological disorders—e.g., multiple sclerosis, Parkinson's disease, or known history of spinal cord injury.Post-rectal surgery or patients with anal atresia.Patients with severe coagulation disorders or with infection.Patients participating in another clinical study or who have been enrolled in another clinical study 4 weeks before randomisation.

##### Withdrawal Criteria

The participants can quit between the signing of informed consent and random assignment because of any of the following reasons:

Participants do not meet with the eligibility criteria.Participants decide to withdraw the informed consent.Researchers consider participants unsuitable to continue with the study.

### Procedures

#### Treatment Allocation and Blindness

Confirmation of the study eligibility is required before patients are randomly assigned to receive treatment. The investigator will review the screening procedure and confirm that the patient meets all the inclusion criteria and does not meet any of the exclusion criteria. Subjects willing to randomise will be enrolled in the RCT cohort and assigned to the TURP or TPLA treatment at 1:1 randomly. Computer-generated random numbers applied. The stratified block randomisation will be applied using the Interactive Web Response System (IWRS; URL: https://jcri.shsmu.edetek.cn/actims_ngm_V2/login.action), which was designed by Clinical Research Institute of Shanghai Jiao Tong University School of Medicine (Shanghai, China). The stratification factors include study sites and severity of BPH (according to the baseline IPSS score, 8–19 as moderate, and 20–35 as severe). Study sites will conduct competitive enrolment with four as the minimum sample size requirement. Because the trial is open-label, both the patients and the surgeon are aware of the treatment allocation, but the outcome evaluations are performed by blinded readers.

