#### Statistical Methods

We will report our results according to the CONSORT 2010 Statement (44).

The demographic and clinical characteristics of subjects in TPLA/TURP arms will be described. The qualitative variables will be presented as absolute numbers and proportions. Quantitative variables will be presented as the means ± SD or medians and IQRs as appropriate.

The primary endpoint, the IPSS score change at 3 months from baseline, will be compared using the Mann–Whitney *U*-test or Student's *t*-test as appropriate. The safety endpoint, the incidence of complications within 3 months after surgery, will be compared using the χ^2^ test. The primary analysis will be performed on the ITT set defined as all patients who meet the eligibility criteria and undergo randomisation. Predefined subgroup analysis includes the age group, BPH severity according to the baseline IPSS score, the sites grouped by country. Missing values will be imputed with multiple imputations under the assumption of missing at random except for the safety endpoints. All statistical analyses will be performed using R (version 3.5.1).

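### The primary test of 3-month IPSS change leaves out both factors used to stratify randomisation, which costs precision

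*Protocol article*

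**What the plan says.** Under Treatment Allocation and Blindness, the protocol article states: "The stratified block randomisation will be applied using the Interactive Web Response System". It then adds: "The stratification factors include study sites and severity of BPH". Severity has two levels, set "according to the baseline IPSS score, 8–19 as moderate, and 20–35 as severe". On site size it says: "Study sites will conduct competitive enrolment with four as the minimum sample size requirement". No block size is given.

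The Abstract gives two site counts. Its methods part says: "One hundred and fourteen patients with BPH will be recruited at 19 sites". Its discussion part describes the trial as "including 16 participating centres in China, Italy, Switzerland, and Poland".

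Under Statistical Methods, the primary endpoint (IPSS change from baseline to 3 months) is compared by the Mann–Whitney test or Student's t-test, and complications by a chi-square test. None of these contains a stratification factor or covariate. The only later use of either factor is in subgroups: "Predefined subgroup analysis includes the age group, BPH severity according to the baseline IPSS score, the sites grouped by country". There site appears only after grouping by country.

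**The concern.** Stratifying the randomisation removes part of the between-arm variation in the stratification factors. A two-sample test that ignores those factors still counts that variation as noise. Its standard error is then larger than the true sampling error of the treatment difference, and its confidence interval is too wide.

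Here the omitted factor is close to the outcome. Severity is a cut of baseline IPSS, and the endpoint is the change from that same baseline.

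What is at stake is precision. A non-inferiority conclusion that the data could support may be missed, although the information needed to avoid this is already collected. The small strata add a second reason to adjust: if balance within them is incomplete, a model containing baseline IPSS also corrects the estimate for whatever baseline difference remains.

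**Working it through.** **1. The plan's own figure.** Inputs from Sample Size Calculation: SD 6, margin 3, true difference 0, α = 0.05, β = 0.2, 10% drop-off.
- Normal approximation, one-sided 0.05: n per arm = 2 × 6² × (1.645 + 0.842)² / 3² = 49.5, so 50 per arm, 100 in all.
- The t-based version gives 51 per arm, 102 in all, as stated. 102 / 0.90 = 113.3, so 114.
- One-sided 0.025 gives 126 or 128 and does not reproduce 102. The calculations below therefore use one-sided 0.05.

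**2. Cost of leaving the strata out.** Let R² be the share of outcome variance explained by the strata. The document does not give it, so a range is shown.
- Standard error used by the unadjusted test: SE = 6 × √(2/51) = 1.188.
- True standard error if the strata are balanced: SE_R = SE × √(1 − R²).
- True error of the unadjusted test: 1 − Φ(1.645 × SE / SE_R).
- Power unadjusted: Φ((3 − 1.645 × SE) / SE_R). Power adjusted: Φ(3 / SE_R − 1.645).

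For R² = 0.2: SE_R = 1.188 × 0.894 = 1.063. True error = 1 − Φ(1.839) = 3.3%. Power unadjusted = Φ(1.046 / 1.063) = Φ(0.984) = 84%. Power adjusted = Φ(2.823 − 1.645) = Φ(1.178) = 88%.

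| R² (assumed) | True one-sided error, unadjusted | Power, unadjusted | Power, adjusted | Interval width, unadjusted / adjusted = 1/√(1 − R²) |
|---|---|---|---|---|
| 0 | 5.0% | 81% | 81% | 1.00 |
| 0.1 | 4.1% | 82% | 85% | 1.05 |
| 0.2 | 3.3% | 84% | 88% | 1.12 |
| 0.3 | 2.5% | 85% | 92% | 1.20 |
| 0.4 | 1.7% | 87% | 95% | 1.29 |

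This is an idealised case: strata perfectly balanced and no degrees of freedom lost. With incomplete balance the unadjusted error lies nearer 5%.

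**3. Is R² likely to be more than trivial?** One indication is in the Discussion. A cited single-arm TPLA study reports IPSS of 22.5 ± 5.1 at baseline and 7.7 ± 3.3 at 6 months. The correlation ρ between the two is not given.
- ρ = 0: variance of change = 5.1² + 3.3² = 36.90. The share explained by baseline is 26.01 / 36.90 = 0.70.
- ρ = 0.5: variance of change = 36.90 − 2 × 0.5 × 5.1 × 3.3 = 20.07. Covariance of baseline with change = 8.415 − 26.01 = −17.595. Share = 17.595² / (26.01 × 20.07) = 0.59.

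This concerns continuous baseline IPSS in one arm at 6 months. A two-level cut carries less. It is not an estimate for this trial, but it shows why baseline should be in the model.

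**4. How sparse the strata are.** 16 × 2 = 32 strata, 114 / 32 = 3.6 patients each. 19 × 2 = 38 strata, 114 / 38 = 3.0 each. A site at the minimum of four has about two per stratum.

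Arm imbalance was simulated with 114 patients, 16 or 19 sites, at least four per site and 1,500 runs per scenario. Block size, severe share (50% or 65%) and spread of site sizes are assumptions.

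| Allocation | Non-empty strata that never fill one block | Mean arm difference (patients) | Chance of a difference of 10 or more |
|---|---|---|---|
| Blocks of 2 | 11–17% | 3.0–3.5 | 2–4% |
| Blocks of 4 | 55–67% | 4.3–4.7 | 9–13% |
| Blocks of 6 | 82–92% | 5.0–5.7 | 14–20% |
| Simple randomisation | – | 8.3–8.8 | 39–42% |

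Among severe patients, the SD of the arm difference is 3.7–4.3 with blocks of 4, against 7.6–8.8 under simple randomisation. At 102 evaluable, unequal arm sizes cost little: power is 81.1% with equal arms, 80.7% at a difference of 10 and 79.7% at 20.

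**The case against.** The strongest reply is that covariates are commonly left to the analysis plan, which is not shown, and that the error is in the safe direction: a false claim of non-inferiority becomes no more likely. The second half stands in full. The first stands in part. An analysis plan may add the terms, but the article is not silent: it names two unadjusted tests for the primary endpoint.

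A second reply is that the gain rests on an assumed variance share, and that the unadjusted test is conservative only as far as stratification achieved balance. Both are true, which is why a range is shown and the error column is a limiting case. Neither favours the unadjusted test: if balance is poor, adjustment for baseline corrects the estimate instead.

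Three stronger readings are tempting and are not supported.
- *The strata are too sparse for blocks to balance anything.* Block size is not stated, and an article may properly omit it. With blocks of 2 most strata fill at least one block. Even with blocks of 4 or 6, imbalance is roughly half to two-thirds of that under simple randomisation.
- *Open-label sites can predict allocations.* Nothing in the article says that sites know the block size, and small strata mean that blocks of 4 or more seldom reach their forced last places.
- *Site should be replaced as a stratification factor.* The Discussion says that skill differs between centres, which is a sound reason to stratify by site in a surgical trial. Enrolment status is unknown, so the cost of a change cannot be judged.

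**Conclusion.** The point holds as one about precision. The stated primary analysis ignores both factors by which patients are randomised, one of them derived from the baseline of the outcome. To the extent that the strata predict outcome, the interval is too wide and the test conservative. At 102 evaluable and one-sided 0.05, the power given up is about 2 points if the strata explain 10% of variance, 4 points at 20%, 6 at 30% and 7 at 40%, assuming balanced strata and the plan's SD of 6. If the strata explain nothing, nothing is lost.

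The 32 to 38 strata of about three patients weaken balance at block sizes of 4 or more. They do not remove it, and the effect of unequal arm sizes on power is about one point. The two site counts in the Abstract contradict each other and have to be reconciled. This is a worthwhile improvement, not a flaw that threatens the validity of the trial.

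**What to change.** Make the primary analysis a linear model (ANCOVA) of 3-month IPSS change on treatment, with baseline IPSS as a continuous covariate, which carries severity, and site as a random intercept. Country as a fixed effect is the alternative; choose one in advance. At 114 / 19 = 6.0 or 114 / 16 = 7.1 patients per site, fixed effects for every site would spend many degrees of freedom.

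Compare the confidence limit for the adjusted difference with the margin of 3, and state the one-sided level. With change defined so that improvement is negative and the difference taken as TPLA minus TURP, the upper limit must lie below 3. The multiple-imputation model should contain the same terms. The unadjusted comparison can stay as a sensitivity analysis.

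Correct the Abstract so that 19 sites and 16 centres agree, or explain the difference.

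The cost is wording, to be settled before outcome data are compared by arm. No new data, patients or change to the randomisation system is needed.
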